### Hypothesis 2: AI-based clinical decision-making will provide suggestions comparable to a multi-professional care team

4.2

To compare decision-making between the healthcare team (Arm 1) and AI (Arm 2), we will calculate the percentage of identical choices (e.g., arm 1 e-CBT intensity 1 and arm 2 e-CBT intensity) and use a 3 × 3 crosstab analysis (i.e., 3 e-CBT intensities for treatment arm 1 versus 3 e-CBT intensities for treatment arm 2). A chi-square test will be used to evaluate the significance and whether the two models (i.e., healthcare team vs. AI decision) are related or independent. From a machine learning perspective, we will calculate the model’s precision, recall, and F1 score, assuming the healthcare team’s performance level is the baseline level. The precision, recall, and F1 scores provide insight into the quality of the machine-learning model (48).

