## Objectives

2

The primary objective of this study is to evaluate the effectiveness of the suggested level of care made by the AI compared to the healthcare team and the effectiveness of the stratified care model. This will be assessed using the change in the severity of depressive symptoms using the Patient Health Questionnaire – 9 Item (PHQ-9) (35) and Quick Inventory of Depressive Symptoms (QIDS) (36) scores, and the quality of life and functioning using Assessment of Quality of Life (AQoL-8D) (37) scores between the start and the end of the 13-session e-CBT program.

The secondary objectives include evaluating compliance and treatment completion using the number of sessions completed by each participant and evaluating the time and cost commitment of initial assessments (i.e., manual participant stratification by the healthcare team vs. the AI) and the different care intensities (i.e., only e-CBT, e-CBT + phone calls, or e-CBT + video calls). We will also evaluate the functional consequence of our interventions on participant quality of life via Quality-adjusted life years (QALY)s (38). Throughout the study, QALY estimates will be derived from AQoL-8D scores using the area under the curve method (39, 40). Outlined below are the research questions and the corresponding study hypotheses:

1 Will participants with major depressive disorder (MDD) assigned to an e-CBT program by an AI show similar outcomes in depressive symptoms at 3 months to those allocated to an e-CBT program decided by a team of healthcare professionals?

– We hypothesize that the outcomes in depressive symptoms of treatment arm 1 will be comparable to the outcomes of treatment arms 2 and 3 following e-CBT treatment.

2 How does AI-based clinical decision-making compare to that of a multi-professional healthcare team when allocating individuals with depression to an e-CBT program with different degrees of care intensity?

– We hypothesize that AI-based clinical decision-making (treatment arm 2) will provide suggestions comparable to that of a multi-professional care team (treatment arm 1).

3 Is this novel AI approach to e-CBT time and cost-efficient and comparable to the standard multi-professional healthcare decision-making team?

– We hypothesize that the AI approach will decrease the overall time and cost commitment of providing e-CBT.

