## Statistical analysis

4

Initially, all data will be examined for missing, nonsensical, and outlying variables. Missing data will not be attributed and will be treated as missing. All statistical analyses will be performed at the end of the trial and will consider a significance level of 0.05 and 95% confidence intervals. Analyses will be conducted to account for and assess differences across sex and gender identifications, and how these factors affect the adaptability and efficacy of e-CBT.

### Hypothesis 1: outcomes in depressive symptoms of treatment arm 1 will be comparable to treatment arms 2 and 3

4.1

Clinical outcomes of the healthcare teams’ decision (arm 1) versus the AI’s decision (arm 2), will be compared by assessing the treatment completion rate, number of completed sessions, and change in questionnaire scores. The completion rate across the two study arms and three levels of care will be calculated using a 2 × 3 × 2 contingency matrix (i.e., healthcare team vs. AI × 3 different treatment intensities × completers vs. dropouts) and chi-square analysis to compare within and between completion rates in the two arms. We will use a 2 × 3 (i.e., healthcare team vs. AI × 3 different levels of care) two-way analysis of variance (ANOVA) to compare the number of completed sessions across participant groups and care levels. Questionnaires are collected at 3 different times; at the start (for all participants), midway (for those who completed at least 6 sessions), and end of the study (for those who completed the treatment program). We will use a 2 × 3 × 3 (i.e., healthcare team vs. AI × 3 different levels of care × 3 time points) linear mixed-effects model for each questionnaire to compare clinical outcomes within and between groups and times. A mixed-effects model analysis will account for any missing data caused by participant dropout. Finally, we will assess if demographic covariables affect clinical outcomes using multiple 2 × 2 × 3 × 3 (demographic factors (e.g., male vs. female) × healthcare team vs. AI × 3 different levels of care × 3-time points for the questionnaire’s score) mixed-effects model to account for each demographic variable (i.e., sex, gender, age, and income). Bonferroni corrections will follow the ANOVA analyses in *post hoc* analyses.

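### Section 4.2: the agreement rate and the only planned test cannot show whether the AI systematically assigns less or more care than the team

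*Protocol article*

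**What the plan says.** Section 2 (Objectives) sets the target: "We hypothesize that AI-based clinical decision-making (treatment arm 2) will provide suggestions comparable to that of a multi-professional care team". Section 4.2 names the methods.

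- **Agreement rate:** "we will calculate the percentage of identical choices".
- **Crosstab:** a 3 x 3 table of "3 e-CBT intensities for treatment arm 1 versus 3 e-CBT intensities for treatment arm 2".
- **Test:** chi-square, to judge "whether the two models (i.e., healthcare team vs. AI decision) are related or independent".
- **Scores:** "we will calculate the model’s precision, recall, and F1 score, assuming the healthcare team’s performance level is the baseline level". Whether these are per level or averaged over levels is not stated.

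The general rule in section 4 is that analyses "will consider a significance level of 0.05 and 95% confidence intervals". Section 4.2 gives no threshold or margin for comparable, and no test of symmetry or of equal margins.

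Three other places matter. Section 3.3 has every participant complete both the team intake assessment and the Triage Module, so a paired table is possible. The same section then restricts analysis to the data of the assigned arm. Section 3.4 describes the third level as e-CBT with pharmacotherapy, but its closing paragraph lists that level as including calls as well.

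**The concern.** The protocol treats the three options as intensities of care, and the allocation rule in section 3.3.2 escalates: neither criterion met, either one met, both met. A disagreement in which the AI chooses less care than the team is therefore a different error from one in which it chooses more. For a triage tool, systematic under-assignment is the error most relevant to safety.

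Percent identical depends on the diagonal alone. The chi-square null is independence, which is neither symmetry nor equal margins, and its value does not change if the table is transposed. An AI that shifts participants one level down is still strongly associated with the team's choice. The headline rate and the only p-value can therefore both look favourable while the AI leans one way.

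**Working it through.** **Inputs.** N = 186 is the planned total (section 3.10) and the maximum for a team-by-AI table. The documents give no joint distribution of the two decisions, so all cells below are assumptions. Hypothesis 2 has no stated figure to reproduce.

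**Tables** (rows team, columns AI, lowest to highest level; team split assumed 62/62/62):
- A, balanced: [48,14,0], [14,34,14], [0,14,48]
- B, mostly lower: [55,7,0], [21,34,7], [0,21,41]
- C, all lower: [62,0,0], [28,34,0], [0,28,34]

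**Percent identical.** The diagonal sums to 130 in each table, and 130/186 = 69.9%.

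**Chi-square** = N[Σ O²/(row total × column total) − 1].
- A: all margins are 62 and Σ O² = 6548, so 186 × (6548/3844 − 1) = 130.8.
- C: the AI margins are 90/62/34 and the sum is 1.8825, so 186 × 0.8825 = 164.1.
- C transposed (all higher) also gives 164.1.

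**Stuart-Maxwell** = d′V⁻¹d on 2 df, where d holds the differences between team and AI margins for two of the levels. In all three tables V = [[28, −28], [−28, 56]], with determinant 784.
- A: d = (0, 0), giving 0.
- B: d = (−14, 0), giving 196 × 56/784 = 14.
- C: d = (−28, 0), giving 784 × 56/784 = 56.

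| | A | B | C |
|---|---|---|---|
| AI lower / higher | 28 / 28 | 42 / 14 | 56 / 0 |
| Identical | 69.9% | 69.9% | 69.9% |
| Chi-square | 130.8 | 138.6 | 164.1 |
| Macro precision | 0.70 | 0.71 | 0.75 |
| Macro recall | 0.70 | 0.70 | 0.70 |
| Macro F1 | 0.70 | 0.70 | 0.69 |
| Kappa / linearly weighted kappa | 0.55 / 0.66 | 0.55 / 0.66 | 0.55 / 0.66 |
| Recall by level | 0.77, 0.55, 0.77 | 0.89, 0.55, 0.66 | 1.00, 0.55, 0.55 |
| Precision by level | 0.77, 0.55, 0.77 | 0.72, 0.55, 0.85 | 0.69, 0.55, 1.00 |
| Sign test p | 1.0 | 0.0002 | 3e-17 |
| Stuart-Maxwell | 0 | 14 | 56 |

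Every chi-square p-value is below 1e-26. Kappa does not separate the tables either, so an agreement index alone would not cure this.

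**Sensitivity to the assumed cells.** With some two-level disagreements, [44,14,4], [14,34,14], [4,14,44] against [58,4,0], [26,34,2], [6,26,30], identity is 65.6% in both. Chi-square is 96.8 against 121.2, and Stuart-Maxwell 0 against 41.2.

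With an unequal assumed team split of 61/98/27, [41,18,2], [18,71,9], [2,9,16] against [59,2,0], [34,62,2], [3,17,7], identity is 68.8% in both. Chi-square is 93.4 against 101.2, and Stuart-Maxwell 0 against 42.2. Here macro F1 does fall, from 0.66 to 0.61, without indicating a direction. Recall for the highest level falls from 0.59 to 0.26.

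**The case against.** The strongest reply is that the plan already contains the direction. The crosstab displays it: in table C the AI margins of 90/62/34 sit beside the team's 62/62/62. Precision and recall in a three-class problem are often given per class, and then they reveal it. This stands. A reader might infer that every Hypothesis 2 summary is blind to direction, or that a biased and a balanced AI score the same. Neither holds: macro precision and chi-square also differ between the tables. What remains is that no planned test addresses direction and that per-level reporting is not stated.

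Second, the article is condensed, and extra agreement tests may be left to a fuller plan. That would answer a plain omission. Section 4.2, however, names a specific test for this hypothesis, and that test cannot answer it.

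Third, too little care would show in the randomised comparison of outcomes in section 4.1. This is a partial safeguard, but it answers Hypothesis 1, not whether the suggestions are comparable.

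Fourth, the ordering of levels 2 and 3 is open to dispute while section 3.4 describes the third level in two ways. In table C, 28 of the 56 disagreements are between those two levels. This stands as a limit on lower/higher counts and on the sign test. Stuart-Maxwell needs no ordering.

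**Conclusion.** The point holds in a limited form. The headline rate and the sole test in section 4.2 do not address systematic under- or over-assignment, and averaged scores would largely hide it. An AI that under-assigns could be reported as comparable with the same agreement rate as a balanced one and, in these tables, a larger chi-square (164.1 against 130.8). The invariance of percent identical to the direction of disagreement is general. The rise in chi-square, and the exact equality of kappa and macro recall in tables A to C, belong to the assumed cells and the equal team split.

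Two stronger inferences are not supported. One is that such an AI would be declared comparable: section 4.2 contains no decision rule, so it could be, not would be. The other is that a shift to lower care would produce the saving expected under Hypothesis 3. The cost analysis in section 4.3 has care level as a factor and counts assessment time, so that link is not shown.

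The change is worth making before analysis.

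**What to change.** Add to section 4.2, on the paired table of team and AI decision for the same participant:

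1. The proportion for whom the AI chose a lower level than the team, and the proportion for whom it chose a higher level, each with a 95% confidence interval.
2. A Stuart-Maxwell test of marginal homogeneity, read with the two sets of margins, or a sign test on the discordant pairs.
3. Precision and recall by level.
4. A statement that comparability will not be claimed from percent identical or the chi-square test alone. A non-significant Stuart-Maxwell or sign test should not count as proof of comparability either; the intervals in item 1 carry that judgement.

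Reconcile two places. Section 3.3 limits analysis to the assigned arm's data, whereas the paired comparison needs both decisions for each participant. Section 3.4 must say consistently whether the third level includes calls, because the ordering of levels 2 and 3 depends on it.

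The cost is a few lines of text and one more table. No data are needed beyond the two assessments that every participant already completes. The conclusion may be less favourable to the AI.

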### Study design

3.3

If eligible for this randomized controlled trial, participants (*n* = 186) will be randomized (Figure 1) to receive an e-CBT treatment recommended by a multi-professional healthcare team consisting of a psychiatrist, psychiatric medical resident, and a trained research assistant (Arm 1, control group; *n* = 93), or the AI machine learning algorithm (Arm 2, experimental group; *n* = 93; Figure 1). To ensure blinding, all participants will complete the intake assessment by the healthcare team (Arm 1) and the Triage Module (Arm 2). Only the relevant data (i.e., Arm 1: intake assessment vs. Arm 2: Triage Module) will be analyzed depending on the treatment arm that the participant is randomly assigned to.

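### Hypothesis 2 needs the team's and the AI's decision on the same participant, but Section 3.3 restricts analysis to one of them, and the only test named for it measures association, not agreement

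*Protocol article*

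**What the plan says.** The protocol article's Section 2 (Objectives) hypothesizes that the AI "will provide suggestions comparable to that of a multi-professional care team (treatment arm 1").

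For this, Section 4.2 (Hypothesis 2) states that "we will calculate the percentage of identical choices" and that the analysts will "use a 3 × 3 crosstab analysis (i.e., 3 e-CBT intensities for treatment arm 1 versus 3 e-CBT intensities for treatment arm 2"). It adds a chi-square test of "whether the two models (i.e., healthcare team vs. AI decision) are related or independent", and then "precision, recall, and F1 score, assuming the healthcare team’s performance level is the baseline level".

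Section 3.3 (Study design) says that "all participants will complete the intake assessment by the healthcare team (Arm 1) and the Triage Module (Arm 2"), for the sake of blinding. The next sentence reads: "Only the relevant data (i.e., Arm 1: intake assessment vs. Arm 2: Triage Module) will be analyzed depending on the treatment arm" to which the participant was randomized. There are 93 participants in each arm (for example "Arm 2, experimental group; *n* = 93").

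**The concern.** There are two separate problems.

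1. **Pairing.** Every descriptive measure in Section 4.2 compares two decisions about one person. The Section 3.3 sentence, read as it stands, keeps one decision per person. Section 4.2 makes no exception, and it labels the two sides of its table by treatment arm, that is, by two separate sets of people. Team deliberation is described only under Arm 1 (Section 3.3.1) and algorithm scoring only under Arm 2 (Section 3.3.2). No section says that the team records a level for Arm 2 participants or that the algorithm is run for Arm 1 participants.

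2. **The test.** The hypothesis is about similar recommendations. Rejecting independence shows only that the two decisions are related. Two deciders can be strongly related and still differ on most patients, for instance if one tends to choose a higher level than the other.

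At stake is one of the three study hypotheses. It may prove impossible to compute, or a small p-value may be taken as evidence that AI triage matches the team.

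**Working it through.** **Pairs under each reading**

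| Reading of Section 3.3 | Team decision | AI decision | Pairs |
|---|---|---|---|
| Literal: assigned arm's assessment only | 93 (Arm 1) | 93 (Arm 2) | 0 |
| Algorithm also scored for Arm 1 | 93 | 186 | 93 |
| Both decisions recorded for everyone | 186 | 186 | 186 |

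Matching Arm 1 people with Arm 2 people does not rescue the literal reading. Suppose 93 and 93 independent people are paired at random, with the shares used below. The simulated percentage identical averages 40.5% (95% range 30% to 51%) and the chi-square rejects in 5.0% of samples. That is so even if AI and team would agree perfectly on every individual.

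**Inputs for the chi-square check**

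- AI shares from Section 3.3.2: 62/190 = 32.63%, 100/190 = 52.63%, 28/190 = 14.74%. The article's percentages reproduce.
- Assumption: the team has the same shares. The documents give none for the team. The AI shares come from an earlier e-CBT-only sample in which the third level was e-CBT with video call.
- Significance level 0.05 (Section 4); a 3 × 3 table has 4 degrees of freedom.

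**Chance agreement**

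Sum of squared shares: 0.3263² + 0.5263² + 0.1474² = 0.1065 + 0.2770 + 0.0217 = 0.405.

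**Weak agreement**

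Take each cell probability as (1 − κ) × product of the shares, plus κ × the share on the diagonal. With κ = 0.2:

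- Identical choices = 0.2 + 0.8 × 0.405 = 0.524.
- Noncentrality of the chi-square = n × 2κ² = 0.08n, which is 7.44 at n = 93 and 14.88 at n = 186.

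| κ | Identical | Share with p<0.05, 93 pairs | Share with p<0.05, 186 pairs |
|---|---|---|---|
| 0.2 | 52% | about 55% | about 87% |
| 0.3 | 58% | about 90% | over 99% |

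These are simulated rates. At κ = 0.2 and 186 pairs, separate runs gave 85% to 87%. The noncentral chi-square approximation gives 57% (93 pairs) and 89% (186 pairs).

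**Sensitivity to the shares**

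In this construction the noncentrality, 2κ²n, does not depend on the shares, provided that both deciders have the same ones. The percentages do change. With equal thirds, chance agreement is 33.3% and κ = 0.2 means 0.2 + 0.8 × 0.333 = 46.7% identical.

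**Systematic difference (a constructed table of 186)**

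Let the AI choose levels 1/2/3 in 61/98/27 people. The team agrees in 10, 20 and 27 of them and chooses one level higher in the other 51 and 78.

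- Identical: 57/186 = 31%.
- Expected by chance: (61×10 + 98×71 + 27×105)/186² = 0.301.
- Kappa: (0.306 − 0.301)/(1 − 0.301) ≈ 0.01.
- Chi-square: 124.7, p about 5 × 10⁻²⁶.

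**Precision of kappa instead**

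At a true kappa of 0.6 with the same shares, the simulated standard deviation is 0.0746 with 93 pairs and 0.0523 with 186. The 95% half-widths are 1.96 × 0.0746 = 0.15 and 1.96 × 0.0523 = 0.10.

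**The case against.** The restricting sentence stands in a paragraph about blinding. It may have been meant only to say which assessment determines the treatment delivered. Section 4.2 is the specific plan for this hypothesis and presupposes two decisions per person, and the raw assessments are collected in everyone. This much stands: the design does not lack the source data. A reader might infer that comparability can never be shown in this trial, and the documents do not support that. The conflict is between two passages, and wording can resolve it. What remains is that the literal text says the opposite of what Section 4.2 needs, and that completing an intake assessment is not the same as the team recording a level.

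The chi-square is also not the only analysis. Given pairs, the percentage identical, precision, recall and F1 do describe agreement. Section 4.2 nowhere says that p<0.05 would establish comparability. A reader might infer that poor agreement is bound to be reported as success; that is a risk, because this is the only test named, but not a stated plan.

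A reader might also think association is assured because both deciders use the PHQ-9. Some association is to be expected. However, the team also weighs psychiatric, medical and social factors and the algorithm uses free text, so its strength is unknown.

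**Conclusion.** The concern holds for the plan as written. Sections 3.3 and 4.2 conflict: on the literal text there are no paired decisions, although at least 93 pairs, and up to 186, could be formed from assessments that all participants complete. The chi-square addresses a different question from the hypothesis. With kappa at 0.2 it would be significant in about 55% of samples with 93 pairs and about 87% with 186, so significance is no evidence of comparable recommendations.

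These rates assume that the team's shares equal the AI's earlier ones and that disagreement is otherwise random. The mismatch between association and agreement does not depend on either assumption.

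The point should be corrected, but it is not of the highest severity. The symptom and quality-of-life comparisons that form the primary objective are untouched.

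**What to change.** 1. **Section 3.3.** Limit the sentence to which decision sets the treatment delivered, and exempt Hypothesis 2 from it.
2. **Pairs.** State that the algorithm is scored on the Triage Module data of Arm 1 participants, which gives 93 pairs. Add Arm 2 participants wherever the team records a level before allocation is known. This part should be settled promptly: recruitment began in December 2022, and an Arm 2 team level that was not recorded at the time cannot be rebuilt free of knowledge of the allocation.
3. **Section 4.2.** Replace the chi-square by Cohen's kappa with a 95% CI, beside the percentage identical. Keep precision, recall and F1 as descriptive.
4. **Weighting.** Use a weighted kappa only after the third level is reconciled. The list in Section 3.4 gives e-CBT plus pharmacotherapy, while the closing paragraph of that section also includes the call. Until the two agree, the ordering of the levels is not settled.
5. **Optional.** A marginal-homogeneity test (Stuart-Maxwell) would show whether one decider systematically allocates higher or lower.

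The cost is wording in two sections and running the algorithm on Triage Module text, assuming that it is stored. Randomization, sample size and the primary analysis do not change.

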### Hypothesis 3: the AI approach will decrease the time and cost commitment of providing e-CBT

4.3

The cost of initial assessments (i.e., manual participant stratification by the healthcare team vs. the AI) and the different care intensities (i.e., only e-CBT, e-CBT + calls, or e-CBT + pharmacotherapy) will also be evaluated. These costs will be evaluated from a health sector and societal perspective (38). For this analysis we will use (1) healthcare costs paid by the government of Ontario as well as healthcare utilization costs self-reported by participants using a resource-use questionnaire (39, 40); (2) medical and productivity costs due to work absence, evaluated using the Questionnaire on Healthcare Consumption and Productivity Losses for patients with a Psychiatric Disorder (TiC-P) (49); (3) intervention costs including staff time-commitment to deliver interventions, development and maintenance costs, and time commitment to assess and enroll participants into the online program. The costs will be expressed in Canadian dollars (CAD). We will use a 2 * 3 (i.e., healthcare team vs. AI * 3 different levels of care) two-way ANOVA to compare costs within and between arms.

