#### Treatment arm 1: healthcare team allocation

3.3.1

Allocation of treatment intensity by the multi-professional healthcare team will be based on the following criteria:

The severity of symptoms/disability (DSM-5 criteria).Mental health factors (prior treatments and responses, current and past psychotic/manic episodes, current and past suicidal/homicidal ideation/attempts, family mental health history, past psychiatric history, and hospital admissions).Medical factors (current medical conditions and medications, personal and family medical history).Social factors (support system and living situation, and occupational, social, and personal functional impairment).

To assess the severity of MDD symptoms and the functional impairments, participants will complete the PHQ-9 and Sheehan Disability Scale (SDS) (42, 43) before the assessment appointment. The trained research assistant on the multidisciplinary team will conduct the assessment appointment and will relay the information to the rest of the team later to deliberate on treatment intensity allocation. All assessments will occur virtually through phone and video calls. Together, the healthcare team will decide whether the participant should be assigned to the e-CBT-only treatment, e-CBT treatment with weekly phone/video calls, or e-CBT treatment with pharmacotherapy. This process mimics the current triage process in clinical settings. To track cost-effectiveness, the trained research assistant will track the total duration of the individual assessment and team deliberation meetings for analysis of the total time commitment per patient.

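### Hypothesis 3 claims savings in time and cost, but section 4.3 names a test only for costs in CAD, by an ANOVA that splits the arms by care level

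*Protocol article*

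**What the plan says.** The Objectives section of the protocol article states the hypothesis for research question 3: "We hypothesize that the AI approach will decrease the overall time and cost commitment of providing e-CBT". One of its secondary objectives is "evaluating the time and cost commitment of initial assessments", and the same for the care intensities.

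Section 3.3.1 (Treatment arm 1) has the research assistant "track the total duration of the individual assessment and team deliberation meetings for analysis of the total time commitment per patient".

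Section 4.3 carries time and cost in its heading. Its text then says that the cost of initial assessments and of the care intensities will be evaluated, from a health-sector and a societal perspective. It lists three groups of inputs:
- publicly paid care and self-reported healthcare use;
- medical and productivity costs from work absence;
- "intervention costs including staff time-commitment to deliver interventions, development and maintenance costs", together with "time commitment to assess and enroll participants into the online program".

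The unit is the Canadian dollar. The one test named is a 2 × 3 (arm by care level) "two-way ANOVA to compare costs within and between arms".

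**The concern.** The hypothesis has two halves, and the stated test addresses one of them. Staff time is the quantity that the triage method acts on most directly: the team's assessment and deliberation on one side, the Triage Module on the other, and then the therapist time that follows from the allocated intensity. In section 4.3 it appears only after conversion to dollars, listed with healthcare use and productivity loss, which can differ between people for reasons unrelated to triage.

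The form of the test matters too. Care level is decided after randomisation, by the very process under comparison. A model with care level as a factor estimates the arm difference at a given level. The hypothesis concerns the overall commitment of providing e-CBT under each triage method, and that includes whether one method sends fewer people to the more staff-intensive levels.

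At stake is the answer to one of the trial's three research questions. The named test could show no arm difference in cost while staff time per participant did differ.

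**Working it through.** **1. Stated aim against stated test.**

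| Place | Time | Cost |
|---|---|---|
| Objectives, secondary objective | named | named |
| Objectives, hypothesis for question 3 | named | named |
| Section 3.3.1 | recorded for analysis per patient | reason given for the tracking |
| Section 4.3, heading | named | named |
| Section 4.3, outcome and test | only as a priced input | CAD, 2 × 3 ANOVA |

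Time is named everywhere except in the outcome and test.

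**2. What the ANOVA can see.** Let p(a,k) be the share of arm a at care level k, and c(a,k) the mean staff time or cost there, triage included. The mean of arm a is Σ p(a,k)·c(a,k). With p̄ and c̄ the averages of the two arms, the difference between arms splits exactly into

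Σ p̄(k)·[c(2,k) − c(1,k)] + Σ c̄(k)·[p(2,k) − p(1,k)].

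The first term is the within-level difference, and a saving in triage time itself falls there. The second term is the allocation difference. If the arms cost the same at each level, the ANOVA's level-adjusted arm effect and its interaction are both zero in expectation, whatever the second term is.

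**3. Would allocation be balanced?** If both arms had the same level mix, the second term would vanish. The sample size section plans 31 per level per arm, that is 31/93 = 33.3% each. Section 3.3.2 reports that the algorithm split 190 earlier participants 62, 100 and 28, or 32.63%, 52.63% and 14.74%. Applied to 93 people this is about 30, 49 and 14. The cells are set by triage and need not be equal, nor need they match the team's.

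**4. Size of the allocation term in call minutes.** Section 3.4 gives one call of 15–20 minutes per intervention week, and the program has 13 weekly sessions. A participant who takes every call uses 13 × 15 = 195 to 13 × 20 = 260 minutes. Assume, for illustration, that one triage method sends 10 percentage points fewer people to the call level and more to e-CBT only. Mean call time per participant then falls by 0.10 × 195 = 19.5 to 0.10 × 260 = 26 minutes. As a low case, let only the 45% completers assumed in the sample size section take any calls: 0.45 × 19.5 = 8.8 to 0.45 × 26 = 11.7 minutes. The 10 points are an assumption; the article predicts no difference in allocation.

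**5. Masking within total cost.** With 93 per arm and two-sided 0.05 (sidedness assumed), the difference detectable with 80% power is (1.960 + 0.842) × √(2/93) = 0.41 SD. Turning this into dollars or minutes needs an SD, and the article gives none. The sample size rests on PHQ-9 change and says nothing about time or cost.

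**6. Attribution of triage time.** Section 3.3 has every participant go through both the team intake and the Triage Module to preserve blinding. The triage time actually spent is therefore not separated by arm, and an endpoint has to count the minutes of the assigned pathway. Duration tracking is described only under Arm 1.

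**The case against.** The best defence is that time has not been dropped. Delivery time and assessment time are both priced and enter the costs under test. Section 3.3.1 says outright that durations are recorded for a time analysis. This is a condensed article, and the method for a secondary outcome is commonly left to the full protocol or the analysis plan. All of that stands. A reader might infer that the time half of Hypothesis 3 is never tested; the article does not support this, since it announces a time analysis and leaves only the method unstated.

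Masking is not established either. Section 4.3 says that the cost of initial assessments will be evaluated, and nowhere says that all components are pooled into one tested total. If triage cost is compared by itself, most of the masking goes. It is also tempting to attach a power figure, but any such figure comes from the assumed inputs. In a simple two-group comparison with 93 per arm, an assumed saving of CAD 400 has power of about 1.00 if the SD is CAD 500 and about 0.08 if it is CAD 5,000.

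Development cost might be thought to distort the arm comparison. The article does not say that it differs by arm or how it is apportioned, so no point can rest on it.

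Finally, the wording of the test includes a comparison between arms, and an ANOVA with arm entered first would give the unadjusted contrast. The article does not say this. A two-way model with unequal cells, read in the usual adjusted way, gives the level-adjusted contrast.

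What survives is that the analysis the article does specify for Hypothesis 3, down to inputs, currency, factors and test, is in dollars only and is structured by an output of triage.

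**Conclusion.** The point holds in a limited form. Section 4.3 names a test only for costs in CAD, with staff time folded in, and the time analysis announced in section 3.3.1 has no stated outcome or test. The 2 × 3 structure sets aside any saving that comes from different allocation. This rests on the text and on the decomposition above, read with the usual level-adjusted arm effect.

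The extent of masking cannot be quantified from the documents. The 8.8 to 26 call minutes per participant show only that the allocation term need not be trivial; they depend on an assumed 10-point difference in allocation. The point concerns a secondary objective. It changes neither the sample size nor the analysis of depressive symptoms. It is worth acting on because a comparison of everyone as randomised answers Hypothesis 3 more directly than the stated ANOVA, at little cost.

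**What to change.** In section 4.3:
- Name staff minutes per participant as an outcome of Hypothesis 3. Report triage minutes of the assigned pathway and delivery minutes (feedback, calls, other staff contact) separately and in total. The separate reporting matters because delivery minutes vary with allocated intensity and dropout, and could obscure a difference in triage minutes.
- Compare all participants randomised to the AI with all randomised to the team, without care level in the model, and give the mean difference with a 95% CI. The 2 × 3 ANOVA can stay as a description by care level.
- Report the corresponding staff cost separately from utilization and productivity costs.
- State that staff time is recorded in the same way for both pathways.

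The cost is some wording and one more reported secondary endpoint. Staff time is already an input to intervention cost, so little new data should be needed beyond making sure that triage time is logged for the AI pathway too.
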